### Visit schedule and assessments

Patients should be followed up every six months – at least once per year. At this visit, relevant information since the last documentation is collected.

Documentation of data from visits can be performed at the clinic or remotely (e.g., via telephone or video chat), however, such data must be part of the patient charts (exception: data from patient-related outcomes questionnaires, if applicable). For the data collection, the following types of forms are available: inclusion, follow-up, medication, safety reporting.

Owing to the observational study type, no additional or specific visits, tests or assessments are required for the purposes of this registry.

Table 2 lists all tests and assessments recordable at the various time points, if performed on a routine basis.

**Table 2 Tab2:** Assessments

Parameters (if appropriate/if performed)	Inclusion documentation	Follow up documentations every 6 months
Date of documentation	By EDC	By EDC
Date of Informed Consent	X	
Date of visit / contact with patient	X	X
Eligibility criteria	X	
Demographics	X	
Physical examination	X	X
ILD characterization Baseline information (diagnostic procedures) Symptoms Etiology	X	X
Diagnostic procedures HRCT (details t.b.d.) Other	X	X
Lung function FVC DLco FEV1, other	X	X
Exercise capacity 6-min walk distance	X	X
Concomitant diseases	X	X
Treatment History Current medication for ILD (immunosuppression, antifibrotic) Concomitant medication (anticoagulation etc.) O2 Non-pharmacological management	X	X
QoL 0–100 VAS Other instruments in substudies	X	X
Clinical events Exacerbations Hospitalization due to ILD Cardiovascular events Deaths		X
Laboratory assessments, including CRP LDH Differential blood cell count (lymphocytes, neutrophils, eosinophils, monocytes), BAL differential cell count (as available)	X	X
Safety Reporting for nintedanib Adverse Drug Reactions Fatal Adverse Events Pregnancy	X	X
Survival status		X

For exacerbations, the updated classification of exacerbations as issued by the International Working Group Report is used in a modified version [15].

Medications will be documented in detail in terms of drug name and daily dose. Relevant concomitant medications will be documented with generic drug name (INN) or trade name, dosage and with start and stop dates. ILD treatment may be interrupted or prematurely discontinued. In such cases the patient can remain in the registry.

Information on non-pharmacological therapy will be collected in categorial terms (e.g., physiotherapy).

Quality of life on a generic 0–100 numerical scale will be assessed. Other instruments/ questionnaires may be added during the course of the registry.

Patients should be followed up as long as possible (until termination of the registry or death). Patients can stay in the registry irrespective of therapy decisions (if drug therapy is switched, escalated or completely withdrawn), and also after lung transplantation.

Every patient has the right to withdraw participation at any time without giving any reason. Patient will be informed about this right in the Informed Consent form. Data collected up to the time of withdrawal will be used in the analysis and included in the clinical registry report.

Reasons for discontinuation of patients in the registry will be reported as on a follow-up documentation form (end-of-observation visit, EOO). Reasons include lost to follow-up, physician decision, patient decision (e.g. informed consent withdrawn) or administrative reasons. In case of lost-to-follow up, efforts should be made to contact the patient (by phone or other channels) in order to collect missing information.

Regardless of the reason, all data available for the subject up to the time of discontinuation should be recorded on the appropriate eCRF.

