## Objectives and endpoints

The objectives and corresponding endpoints of the registry are shown in Table 1.

**Table 1 Tab1:** Objectives and endpoints

	Objectives	Endpoints
Primary	To compare various PPF groups and treatment strategies in terms of characteristics and outcomes (lung function, survival, quality of life, other)	Time to progression of disease (any one of the following): Decrease of FVC > 10% predicted within one year Decrease Dlco > 15% predicted plus initiation of LTOT or permanent increase of oxygen flow when LTOT is established within one year Decrease of 6-MWD > 50 m within one year Hospitalization due to respiratory decompensation Death of any cause Change of treatment strategy (stop of anti-inflammatory or antifibrotic therapy, initiation of new anti-inflammatory or antifibrotic therapy or a combination of both)
Secondary	To assess drug utilization	Treatment strategy (immunosuppression, antifibrotic therapy) Dose and dosing schedule Duration of treatment (persistence) Switches between treatments Phases without drug treatment (with reasons) Reasons for drug discontinuation
	1. To determine risk factors for progression of disease 2. To determine factors for treatment success or failure, respectively, defined as clinical, functional, and radiographic stabilization (i.e. absence of deterioration in each of the categories) and change of treatment strategy (i.e. stop/start of antifibrotic therapy; stop/start of immunosuppressive therapy)	Survival Clinical symptoms Dyspnea Cough Lung function Annual DLCO decline Annual FVC decline 6-min walk distance QoL scores over time Radiographic course: fibrosis on HRCT Therapy escalation Clinical events (exacerbations, hospitalisations) Analyses stratified according to different diagnosis groups
	3. To determine potential biomarkers, which are routinely measured in many centers, to differentiate inflammatory driven from fibrosis driven progress	Laboratory parameters: CRP LDH Differential blood cell count (lymphocytes, neutrophils, eosinophils, monocytes), BAL differential cell count (as available)
	To assess safety	Adverse Events Adverse Drug Reactions

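### Half of the primary endpoint's components need a discretionary test, so unequal testing between groups can bias time to progression unless the analysis deals with it

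*Protocol article*

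**What the plan says.** All references are to the Protocol article.

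- **Objective.** Table 1 (Objectives and endpoints) gives the primary objective as "To compare various PPF groups and treatment strategies in terms of characteristics and outcomes".
- **Endpoint.** The primary endpoint in Table 1 is "Time to progression of disease (any one of the following"), followed by six components. Three need a test: "Decrease of FVC > 10% predicted within one year"; "Decrease Dlco > 15% predicted plus initiation of LTOT or permanent increase of oxygen flow"; and "Decrease of 6-MWD > 50 m within one year". The other three need no lung-function or walk test: respiratory hospitalisation, death, and change of treatment strategy.
- **Testing.** The Design section leaves every examination to the physician's judgement and usual practice. Visit schedule and assessments states: "Owing to the observational study type, no additional or specific visits, tests or assessments are required for the purposes of this registry". Table 2 lists tests that may be recorded when routine care includes them. Follow-up is meant to be six-monthly, with once a year as the minimum.
- **Remote contact.** The same section says "Documentation of data from visits can be performed at the clinic or remotely (e.g., via telephone or video chat", on condition that the data are held in the chart.
- **Treatment success.** Table 1 (secondary objective 2) defines it as clinical, functional and radiographic stabilisation, meaning "absence of deterioration in each of the categories". HRCT is among the tests recorded only if performed.
- **Analysis.** Descriptive analysis and statistical testing assigns survival and clinical events to Kaplan-Meier estimates and Cox models. Multiple imputation is named among further methods but is not tied to the primary endpoint.

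**The concern.** Under an any-one-of rule, a component that was not measured cannot trigger the event. If one comparison group, or the sites that supply most of it, tests less often, that group has fewer chances to be seen progressing. Its curve then looks better for a reason unrelated to disease or treatment. Sites include both hospitals and office-based practices, so different testing routines are plausible.

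Test timing matters too. The functional criteria apply within one year, while follow-up may be annual. For a patient seen yearly, one omitted test can remove the pair of values needed to judge the component at all.

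Treatment success is exposed in the same way. A patient without a repeat HRCT has no recorded radiographic deterioration, and could be scored a success on a category nobody examined.

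At stake are the comparisons of diagnosis groups and treatment strategies that form the primary objective. The SAP can set a censoring rule, but it cannot recover why a test was not done if that was never collected, and Table 2 lists no such item.

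**Working it through.** **1. The plan's own figure.** There is none on this point. The article gives no expected progression rate, testing rate, effect size or power for the comparison. Its only calculation, the rule of three for adverse drug reactions, does not bear on it.

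**2. Inputs.** From the article: six components, three of them test-dependent; no required test; a target of 900 patients. Assumed, because the article does not give them:

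- *f*, the one-year risk of truly meeting a functional component: 0.10 to 0.30
- *h*, the one-year risk of a test-free component, independent of *f*: 0.10 to 0.30
- *t*, the proportion adequately tested: 90%, 70% or 50%, and unrelated to true risk
- two groups of 450 with identical *f* and *h*
- untested patients left in the risk set without an event

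**3. Formula.** Observed one-year progression = 1 − (1 − *h*)(1 − *f·t*). The spurious cumulative-hazard ratio is ln(1 − risk in the less-tested group) / ln(1 − risk in the more-tested group).

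**4. Central case, *f* = *h* = 0.20.** The true risk in both groups is 1 − 0.80 × 0.80 = 36.0%.

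- 90% tested: 1 − 0.80 × (1 − 0.18) = 34.4%
- 70% tested: 1 − 0.80 × (1 − 0.14) = 31.2%
- 50% tested: 1 − 0.80 × (1 − 0.10) = 28.0%

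| Testing | Observed progression | Spurious ratio | Two-sided 5% test favours the less-tested group |
|---|---|---|---|
| 90% v 90% | 34.4% v 34.4% | 1.00 | 2.5% (nominal) |
| 90% v 70% | 34.4% v 31.2% | ln 0.688 / ln 0.656 = 0.89 | 17% |
| 90% v 50% | 34.4% v 28.0% | ln 0.720 / ln 0.656 = 0.78 | 55% |

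**5. Range.** Over *f* and *h* from 0.10 to 0.30, the ratio is 0.81 to 0.95 for 90% v 70% and 0.64 to 0.91 for 90% v 50%. It moves towards 1 as test-free events make up more of the total.

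**6. 6-MWD alone.** Assume 8% to 15% of patients a year would progress on 6-MWD only. The false difference is the gap in testing times that risk:

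- 80% v 40% tested: 0.40 × 0.08 = 3.2 points to 0.40 × 0.15 = 6.0 points
- 70% v 50% tested: 0.20 × 0.08 = 1.6 points to 0.20 × 0.15 = 3.0 points

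**7. Interval.** If a decline starts at a uniformly distributed time between tests, it is found on average half an interval late: 3 months with 6-monthly tests and 6 months with yearly tests. Groups that differ in interval therefore differ in recorded event time even when every patient is eventually tested.

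**The case against.** The other side has several good points.

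- **No rule is stated for untested patients.** A reader might infer that an untested patient counts as not progressing. The article does not say so. It refers missing-data measures to the Data Management Plan and calculated variables to the SAP, and it names multiple imputation. The inferred rule is only what Kaplan-Meier or Cox produces when nothing else is specified. This stands, so the point is conditional.
- **Remote documentation does not mean a missing test.** A reader might take the telephone and video provision to show that results are lost. The sentence concerns documentation and requires the data to be in the chart, so a clinic spirometry result can be entered after a telephone contact. This stands. The weight rests on discretionary testing, not on remote contact.
- **Testing may be fairly complete.** There is a mandatory data set whose content is not shown, sites have ILD expertise, and eligibility needs a DLco value. All true, but a baseline value does not secure a follow-up value, and the article says that no test is required.
- **Testing habits need not dominate the result.** Three components need no test and may catch deteriorating patients who were not tested. The DLco component also needs an oxygen-therapy change, so a missed DLco loses fewer events than its threshold alone suggests. For the antifibrotic comparison, lung function and 6-MWD go into weighted linear mixed models of observed values, which do not score a missing test as stability. This limits the size. It does not remove the problem for the time-to-progression composite.
- **Discretionary testing is inherent in a registry described as mainly descriptive.** That is so, and no added test is asked for. The primary objective is nevertheless comparative.

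That sicker patients are tested less often is plausible, but the article does not document it.

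**Conclusion.** The point holds in a conditional form. A comparative primary objective rests on an any-one-of endpoint in which three of six components depend on discretionary tests at intervals that may differ. The article fixes no minimum assessment for that endpoint. Unless the analysis handles this, differences in testing between groups or sites can bias the comparison in favour of the less-tested group. Treatment success has the same weakness where HRCT is not repeated.

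The size cannot be derived from the article. Under the assumptions above, the spurious ratio is 0.81 to 0.95 for 90% v 70% testing and 0.64 to 0.91 for 90% v 50%. It is 1.00 if testing is equal. These figures also rest on untested patients staying at risk and on testing being unrelated to true risk.

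The article does not support saying that untested patients are classified as stable by rule, that remote contacts cause the loss, or that testing habits determine the result.

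**What to change.** 1. **Record test status.** At each follow-up from now on, record for FVC, DLco, 6-MWD and HRCT: done; not done, not scheduled or remote; not done, patient unable because of ILD.
2. **Report testing.** Show testing frequency and interval by comparison group beside every between-group result.
3. **Keep the stated composite and add sensitivity analyses:**
   - censor the functional components at the last adequate test, or use interval-censored methods;
   - use only the components that need no test (death and respiratory hospitalisation), with and without treatment change;
   - count inability to perform the test because of ILD as functional progression.
4. **Treatment success.** Do not score it on categories that were not measured.

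Censoring at the last test belongs among the sensitivity analyses: if tests are missed because of illness, that censoring is itself informative. This is also why the reason for a missed test has to be collected.

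**Cost.** One extra eCRF item per test and SAP wording; no added visit or test. Reasons cannot be recovered for visits already documented in the first 360 patients (status at 11 January 2023, of 900 planned). The censored and test-free analyses will have fewer events, and fewer patients will be evaluable for treatment success.

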## Safety reporting

Due to sponsor obligations, serious and non-serious adverse drug reactions (ADR), fatal adverse events (AE), and pregnancies in female patients (and in partners of male patients) in all patients receiving nintedanib must be reported by investigators to Boehringer Ingelheim. The described events are to be reported by the electronic data entry form on the website of the INSIGHTS-ILD registry. In case the electronic system should not be accessible, the investigator may alternatively use paper sheets which should be sent via fax to Boehringer Ingelheim.

Serious ADR and fatal AE must be reported within 1 business day after knowledge. Non-serious ADR (e.g., all ADR that do not meet the definition of serious) and pregnancies should be reported within 7 business day after knowledge.

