## Statistical considerations

### Sample size

As the present registry has mainly descriptive aims, there is no formal power calculation needed to determine the target sample size [17]. Rather, the sample size is determined by feasibility aspects.

From a drug safety angle, an enrolled number of 900 patients according to the “rule of three” will allow for the detection of ADR occurring at an incidence of 1 in 300 person-years [18, 19]. If the median observation duration is 2.5 years, an ADR occurring with an incidence of 1 in 750 person-years will be detected.

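### Adverse drug reactions are recorded only under nintedanib, but the detection limit uses all 900 patients and Table 1 sets unrestricted adverse-event endpoints

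*Protocol article*

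**What the plan says.** Four parts of the protocol article bear on this.

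- **Objectives and endpoints, Table 1.** The safety objective has the endpoints "Adverse Events Adverse Drug Reactions". No drug, seriousness or outcome limit is attached. The Rationale and aim section likewise speaks of medication safety in general.
- **Sample size.** The statement starts from "an enrolled number of 900 patients according to the" rule of three, which "will allow for the detection of ADR occurring at an incidence of 1 in 300 person-years". It continues: "If the median observation duration is 2.5 years, an ADR occurring with an incidence of 1 in 750 person-years will be detected".
- **Visit schedule and assessments, Table 2.** The text introduces the table as complete: "Table 2 lists all tests and assessments recordable at the various time points, if performed on a routine basis". Its one safety row reads "Safety Reporting for nintedanib Adverse Drug Reactions Fatal Adverse Events Pregnancy". A separate row for clinical events covers exacerbations, ILD hospitalisations, cardiovascular events and deaths in all patients.
- **Safety reporting.** ADRs (serious and non-serious), fatal adverse events and pregnancies "in all patients receiving nintedanib must be reported by investigators" to the manufacturer.

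The Patients section requires some active therapy but not nintedanib. The section on descriptive analysis and statistical testing names pirfenidone as a second antifibrotic and foresees periods without any antifibrotic.

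**The concern.** The population in whom ADRs are recorded is smaller than the one used to say how rare an ADR the registry can detect. An ADR under pirfenidone, a steroid or another immunosuppressant has no field in Table 2, so patients on those drugs alone add nothing to ADR detection. The 900 in the Sample size section is therefore not the number at risk of a recorded ADR.

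The same gap affects Table 1. Its adverse-event and ADR endpoints read as if they covered the whole registry, but outside nintedanib neither ADRs nor general adverse events are captured.

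Two consequences would follow if the analysis took Table 1 and the Sample size section at face value. An ADR rate divided by all 900 patients would be too low. An ADR comparison between treatment strategies would reflect who has to report, and pirfenidone patients would count as antifibrotic-treated with no ADR capture.

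**Working it through.** **Inputs**
- Enrolment: 900 (Sample size).
- Observation time: one year each is implied by the first limit; a median of 2.5 years is stated for the second (Sample size).
- Population with ADR recording: patients receiving nintedanib (Table 2; Safety reporting).
- Nintedanib share *f*: not given. **Assumption:** 20% to 75%.

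**Step 1: reproduce the stated limits.** By the rule of three, the rate at which at least one event is seen with about 95% probability is 3 / person-years.
- One year each: 900 × 1 / 3 = 300, so 1 in 300. The binomial probability of at least one event in 900 at 1/300 is 0.950.
- 2.5 years each: 900 × 2.5 = 2,250 person-years, and 2,250 / 3 = 750, so 1 in 750. Check: 1 − exp(−2,250/750) = 0.950.

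Both figures reproduce. The arithmetic is sound; the population is the issue.

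**Step 2: use only the patients in whom ADRs are recorded.** With 900 × *f* patients exposed throughout, the limits are
- 1 in 900*f*/3 = 1 in 300*f* at one year each;
- 1 in 2,250*f*/3 = 1 in 750*f* at 2.5 years each.

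The chance of seeing at least one ADR of the claimed rate is 1 − exp(−3*f*) in either case, because 900*f*/300 = 2,250*f*/750 = 3*f*.

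| Assumed share *f* | Patients on nintedanib | Limit, 1 year each | Limit, 2.5 years each | Chance of seeing an ADR of the claimed rate |
|---|---|---|---|---|
| 20% | 180 | 1 in 60 | 1 in 150 | 45% |
| 30% | 270 | 1 in 90 | 1 in 225 | 59% |
| 50% | 450 | 1 in 150 | 1 in 375 | 78% |
| 75% | 675 | 1 in 225 | 1 in 562.5 | 89% |
| 100% | 900 | 1 in 300 | 1 in 750 | 95% |

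**Step 3: exposure time.** The table assumes nintedanib is taken for the whole period. The protocol article expects treatments to be started, interrupted and stopped during follow-up. Person-years on drug are then fewer than 900 × *f* × observation time, and the limits worsen in proportion. Only *f* = 100% with uninterrupted exposure returns the stated figures.

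**The case against.** **Safety reporting as a company duty only.** Read alone, that section could describe just the duty to notify the manufacturer, with other ADRs recorded elsewhere. This does not stand. Table 2 is introduced as the list of everything recordable, and its safety row has the same limit. Even if ADRs of every drug were recorded, 900 would be the right number for a given drug's ADR only if all 900 took that drug.

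**Supplementary statement.** The registry is described as mainly descriptive, and its size is set by feasibility. Correcting the rule-of-three remark changes neither the 900 nor the primary endpoint. This stands, and it limits the severity.

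**Stronger readings.** A reader might infer more than the document supports:
- *That non-fatal events are not collected at all.* Exacerbations, ILD hospitalisations and cardiovascular events are recorded in all patients, and non-fatal ADRs are recorded under nintedanib. Reasons for drug discontinuation, a Table 1 endpoint not tied to one drug, may capture some intolerance.
- *That the safety objective cannot be answered.* Table 1 sets an unrestricted objective but does not promise a safety assessment of each strategy. Deaths and the named events can be described in everyone.
- *That ADRs will be divided by 900 or compared between strategies.* The text specifies neither. The planned antifibrotic yes/no comparison names mortality and lung function, and could include ADRs only under an unspecified remainder of outcomes. Both harms are therefore conditional.

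**Conclusion.** The point holds as an inconsistency. Table 2 and the Safety reporting section confine ADRs, fatal adverse events reported as safety events, and pregnancies to patients on nintedanib. The Sample size statement and the Table 1 safety endpoints are written as if collection covered everyone. What is missing is ADRs and general adverse events outside nintedanib; a limited safety description from deaths and clinical events remains available.

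The stated limits are too favourable by the factor *f*, and by more if treatment is interrupted. The 20% to 75% range is an assumption, so the table illustrates the loss and does not estimate it. The direction is certain for any share below 100%.

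Severity: should be fixed. The detection figures are wrong as written, but they do not determine the size of the registry or its primary analysis.

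**What to change.** 1. **Sample size.** Restate the rule-of-three sentence in nintedanib-exposed person-years. Give the detectable incidence over a range of shares, and say that exposed time, not observation time, is what counts.
2. **Table 1, safety.** Restrict the endpoints to ADRs, fatal adverse events and pregnancies under nintedanib, plus the clinical events and deaths recorded in all patients.
3. **Analysis.** Use nintedanib exposure time as the denominator of any ADR rate. State that ADRs and general adverse events will not be compared between treatment strategies. Leave the planned mortality and clinical-event analyses in place, since their data exist for all patients.

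The cost is wording in the protocol and SAP, a less favourable detection limit and a narrower safety claim. Extending the safety form to all ILD drugs would be an alternative. It adds site work, and because 360 patients were already enrolled by January 2023, ADR data from before the change could be incomplete.
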